**Associations of migrant and socioeconomic status with BMI,**

**gestational weight gain and self-reported health:**

**a population-based study from the Swedish Pregnancy Registry**

**Background**

Excessive body weight and gestational weight gain are important modifiable risk factors for numerous pregnancy outcomes for both mother and child (1). For instance, both overweight/obesity before or in early pregnancy and excessive gestational weight gain has been associated with increased risks for adverse pregnancy health outcomes such as gestational diabetes, preeclampsia, cesarean delivery and infant death (1-4). Conversely, underweight and inadequate gestational weight gain have been associated with higher risks of low birth weight infants and preterm birth (1).

It is well-established that women being born in a foreign country, herein referred to as “migrant women”, have higher risks for severe maternal morbidity as well as maternal and infant death compared to women born in Sweden (5-7). However, it is not known whether the prevalence of unhealthy weight status, GWG and poor self-reported health is different among migrant women or women born in Sweden. It may for instance be hypothesized that for some migrant women the prevalence of unhealthy weight status, GWG and poor self-reported health is more common than among women born in Sweden. However, no such Swedish data is currently available. Furthermore, the few such studies have been conducted globally (for instance; 8-12) have presented mixed findings and majority have been relatively small (9-12). Furthermore, the association of socioeconomic status with weight status, gestational weight gain and self-reported health is relatively unknown, especially in migrant women. Gaining more knowledge in this area is critical since migrant health is a great public health priority and challenge (13, 14) and many countries including Sweden have a steadily increasing migrant population in childbearing age. Indeed, 27 % of women giving birth in 2016 in Sweden were born in another country (15).

The study described in the following application is funded by Forte (dnr: 2017-00088, principal investigator: [name]) and will increase the knowledge regarding the associations of migrant and socioeconomic status with BMI, gestational weight gain and health in a large (> 500 000) population-based cohort of pregnant women with various migrant and socioeconomic backgrounds.

**Specific aims**

The specific aims of this study are to examine associations of i) migrant status ii) socioeconomic status and iii) the combination of migrant and socioeconomic status with

1. BMI and weight status in early pregnancy
2. Gestational weight gain
3. Self-reported health before, during and after pregnancy

**Hypothesis**

We hypothesize that women with migrant background and/or low socioeconomic status have higher pre-pregnancy BMI and gestational weight gain and lower self-reported health before, during and after pregnancy.

**Project description**

**Study design**

Data of exposures, outcomes and covariates (see below) will be retrieved from the Swedish Pregnancy Register for the years 2010 to 2018 and study will include approximately 500 000 women. An internal validation of this registry showed that variables within this registry has overall good to very good degree of coverage, agreement and internal validity (16).

***Main exposure variables***

- Country of birth
- Need of an interpreter in contact with maternity care
- Educational attainment (corresponding to < 9 years, 9-12 years, > 12 years)
- Occupation (work, student, parental leave, unemployed, sick leave/disability pension, others)

***Main outcomes variables***

- BMI, weight and height in early and late pregnancy (kg/m^2^)
- Weight status categories in early pregnancy
- Gestational weight gain between early (at first visit at maternity care) and late pregnancy (after gestational week 35) (kg)
- Gestational weight gain according to IOM recommendations (1)
- Gestational weight gain z-scores (17)
- Self-reported health before, during and after pregnancy

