***Covariates and descriptive variables***

Following variables will be considered as confounders in the analysis and will also be utilized as descriptive data; maternal age, number of previous child labors, previous pregnancies in the Swedish Pregnancy Registry, number of born children in current pregnancy (i.e. single or multiple-pregnancy), length of pregnancy, county council, maternity care unit, smoking, alcohol consumption, type of delivery, infant sex, birth weight and date, stillbirth, dates for visits in maternity care and revisits after birth, educational attainment and occupation, estimated day of birth from ultrasound and last menstruation.

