**Significance**

Migrant health represents a great public health priority and challenge (13, 14) and currently approximately 27 % of pregnant women in Sweden have migrant background (15). Pre-pregnancy body mass index and GWG is a modifiable risk factor for a wide range of pregnancy health outcomes including mortality and severe morbidity in both mother and child (1-4). Hence, this large population based registry study (n > 500 000) will provide novel data of weight status in early pregnancy, gestational weight gain and self-reported health in women with various socioeconomic and migrant background. A distinct study strength is the use of the Swedish Pregnancy Register which has is population-based and has good coverage (16). Furthermore, the large sample size will also allow us to provide data for GWG of migrant women stratified by geographical regions (6), economic status of birth country (7), as well as to examine whether inequalities in GWG can be attenuated by higher educational attainment or occupational status. All of this information is essential, even though the previous literature has demonstrated that migrant women have an increased risk for severe adverse pregnancy outcomes (5-7), less is known whether migrant women have an increased risk of unhealthy weight status, GWG and poor self-reported health.

Altogether, this project will provide evidence whether inequalities regarding weight status, gestational weight gain and self-reported health exist between women with migrant and non-migrant women and/or with low and high socioeconomic status. The data in this described project will therefore contribute to the existing literature. Furthermore, the study has also a great potential to aid in the development of appropriate clinical care and public health polices to promote the health of pregnant women with various socioeconomic and migrant backgrounds.

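### Early-pregnancy BMI has no upper gestational week and is also called pre-pregnancy BMI, so any group difference in timing of the first visit enters the BMI and weight-status comparisons

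*Protocol*

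**What the plan says.** The first aim in the protocol's Specific aims concerns "BMI and weight status in early pregnancy". Main outcomes variables repeats this with "Weight status categories in early pregnancy" and gives no week. The only place that says what early means is the weight-gain outcome: "Gestational weight gain between early (at first visit at maternity care) and late pregnancy (after gestational week 35) (kg". The late weight has a lower limit of week 35, but the early weight has no upper limit.

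The Hypothesis uses a different term. It expects that "women with migrant background and/or low socioeconomic status have higher pre-pregnancy BMI and gestational weight gain". No rule links a first-visit weight to a pre-pregnancy value.

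Covariates and descriptive variables includes "dates for visits in maternity care and revisits after birth" and the estimated day of birth from ultrasound and last menstruation, all to be considered as confounders. Gestational age at first weighing is not named. Length of pregnancy is listed, but that is gestation at delivery. Data analysis and power calculations plans independent t-tests and ANCOVA for continuous outcomes and logistic regression for categorical ones.

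**The concern.** A weight at first visit is body weight before pregnancy plus whatever has been gained by that week. With no upper limit, a woman first seen well into the second trimester contributes an early BMI that includes months of gain. The exposures are country of birth, interpreter need, education and occupation, and timing of first contact with care could plausibly vary with each. If it does, the comparison mixes body size with timing of care.

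This error does not shrink with sample size. In a study of about 500 000 women that counts a difference of 0.07 kg/m² as detectable, a small systematic shift is enough to be declared significant. If the migrant or low-socioeconomic groups were seen later, the shift would run towards the stated BMI hypothesis. The GWG z-scores do not help here, because they address gain and not BMI or weight status.

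**Working it through.** **Inputs from the protocol.** N = 500 000, detectable difference 0.015 SD, power 95 %, α = 0.05, SD of BMI 4.8 (Data analysis and power calculations); 27 % of women giving birth in 2016 were born abroad (Background).

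**Inputs assumed.** The protocol gives no week of first visit by group, no weekly gain and no height. I take height 1.66 m, gain 0.4 kg per week after the first trimester, an excess of 5, 10 or 20 percentage points of late bookers in one group, and 6, 10 or 15 weeks late. Groups are otherwise taken to be equal.

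**1. The plan's own figure.** 0.015 × 4.8 = 0.072 kg/m², which matches the stated 0.07. With a 27 % migrant share, power at 0.015 SD is 99.7 % two-sided rather than 95 %, and the difference detectable with 95 % power is 0.0115 SD. The stated power is therefore conservative, and nothing here turns on it.

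**2. The same figure as body weight.** 0.072 × 1.66² = 0.072 × 2.756 = 0.20 kg.

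**3. Shift in mean BMI with no true difference.** Shift = (excess share of late bookers) × (0.4 kg × weeks late) / 1.66². For one woman 10 weeks late: 4.0 / 2.756 = 1.45 kg/m². For a 10-point excess: 0.10 × 1.45 = 0.145 kg/m².

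| Excess of late bookers | 6 weeks late (2.4 kg) | 10 weeks late (4.0 kg) | 15 weeks late (6.0 kg) |
|---|---|---|---|
| 5 points | 0.044 | 0.073 | 0.109 |
| 10 points | 0.087 | 0.145 | 0.218 |
| 20 points | 0.174 | 0.290 | 0.435 |
| 0 points | 0 | 0 | 0 |

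Of the nine non-zero scenarios, eight reach 0.072 kg/m².

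**4. Chance of a significant result in the smallest scenario.** SE = 4.8 × √(1/365 000 + 1/135 000) = 0.0153 kg/m². Then 0.0435 / 0.0153 = 2.85, and 2.85 − 1.96 = 0.89, so power is about 81 % in an unadjusted comparison.

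**5. A second route, by difference in mean week of first visit.** With height 1.65 m and 0.2 kg per week (both assumed), a one-week difference gives 0.2 / 1.65² = 0.073 kg/m². This would be declared significant with probability 0.998.

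**6. Weight status.** Assume normally distributed BMI with mean 24 to 25 and SD 4.8, and cut-offs at 25 and 30. Moving the whole distribution by 0.07 to 0.3 kg/m² gives spurious odds ratios of about 1.02 to 1.11 for BMI of 25 or more, and 1.03 to 1.13 for 30 or more. For modest shifts few women change category.

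**The case against.** The strongest reply is that the means of adjustment are already in the plan. Visit dates and pregnancy dating are both requested as possible confounders, and together they give gestational age at first visit. ANCOVA and logistic regression could use it, and model detail commonly belongs in an SAP. Part of this stands: it would be wrong to say that the protocol leaves no way to adjust. But a list of dates is not a covariate. The list also includes items that arise after the weighing, such as type of delivery and birth weight, and unadjusted t-tests are planned as well. What a main outcome measures is a protocol matter, and here it is left open at one end and given two names.

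It can also be said that the first-visit gloss belongs to the weight-gain outcome only. That is correct as text; applying it to BMI and weight status is an inference, though no other definition is offered.

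Several stronger readings are tempting but unsupported:

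- A reader might infer that migrant women are classed as heavier through gestational age alone. The protocol has no data on timing by group, so both size and direction are assumed.
- A reader might single out newly arrived women. They cannot be identified from the listed variables.
- A reader might count the Significance sentence beginning "Pre-pregnancy body mass index and GWG is a modifiable risk factor" as a second mislabelling. It is background on published risks, and the same section goes on to describe the study's own data as early-pregnancy weight status.
- A reader might treat 0.07 kg/m² as a threshold of relevance. It illustrates power only; 0.145 kg/m² is about 0.03 SD (0.145 / 4.8).

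**Conclusion.** The point holds in conditional form. The protocol bounds the late weight but not the early one, and its Hypothesis names a pre-pregnancy quantity that the aims and outcomes do not measure. If week of first visit differs between the compared groups, the BMI and weight-status contrasts will partly reflect gestational age at weighing. On the assumptions stated, the shift in mean BMI is about 0.04 to 0.44 kg/m²; with equal timing it is zero. These figures describe comparisons without adjustment for gestational week, and they illustrate possible size rather than estimate a bias known to exist. The matter deserves a change because the study is large enough to declare such shifts significant and already requests the data needed to deal with them.

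**What to change.** - Derive gestational week at first weighing from the visit date and the ultrasound or last-menstruation dating.
- Adjust for it in the BMI model (ANCOVA) and the weight-status model (logistic regression), and treat the unadjusted t-tests as descriptive.
- Add a sensitivity analysis restricted to weights taken within a stated first-trimester limit.
- Report the share of later first visits by migrant and socioeconomic group.
- In the Hypothesis, replace pre-pregnancy BMI with early-pregnancy BMI, so that it agrees with the aims and outcomes.

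The cost is some wording and a little more analysis, with no new data. The restricted analysis applies only to women seen early. If timing does depend on the exposures, restriction could itself select women by exposure, which is why it should be a sensitivity analysis and not the main one.

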***Covariates and descriptive variables***

Following variables will be considered as confounders in the analysis and will also be utilized as descriptive data; maternal age, number of previous child labors, previous pregnancies in the Swedish Pregnancy Registry, number of born children in current pregnancy (i.e. single or multiple-pregnancy), length of pregnancy, county council, maternity care unit, smoking, alcohol consumption, type of delivery, infant sex, birth weight and date, stillbirth, dates for visits in maternity care and revisits after birth, educational attainment and occupation, estimated day of birth from ultrasound and last menstruation.

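### Smoking and alcohol are labelled confounders although, for country of birth and education, they plausibly follow from the exposure

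*Protocol*

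**What the plan says.** - **Role of the covariates.** The section on covariates and descriptive variables opens: "Following variables will be considered as confounders in the analysis and will also be utilized as descriptive data". The list contains "county council, maternity care unit, smoking, alcohol consumption, type of delivery". Nothing sets smoking or alcohol apart from variables such as maternal age, and no variable is named as a possible mediator.
- **Exposures.** The section on main exposure variables lists "Country of birth", need of an interpreter, educational attainment in three bands, and occupation. The occupation categories include unemployment and sick leave or disability pension.
- **Question.** The specific aims ask for associations of migrant status, socioeconomic status and their combination with early-pregnancy BMI and weight status, gestational weight gain and self-reported health. The significance section says that "this project will provide evidence whether inequalities regarding weight status, gestational weight gain and self-reported health exist" between migrant and non-migrant women and between women of low and high socioeconomic status. The one attenuation question posed there is to "examine whether inequalities in GWG can be attenuated by higher educational attainment or occupational status".
- **Methods.** The section on data analysis and power calculations names independent t-tests and analysis of covariance for continuous outcomes, and logistic regression for categorical ones. It does not say which covariates enter which model.

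**The concern.** A confounder is a cause of the exposure, or stands in for one. Smoking and drinking do not determine where a woman was born. In general they do not determine how long she went to school. They are more plausibly among the ways in which background leads to body weight, weight gain and perceived health.

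If a model for country of birth (or the regional and economic groupings built on it) or for education conditions on them, its coefficient answers a different question: does a difference remain among women who smoke and drink alike? The protocol does not ask that. Its only attenuation question concerns education and occupation.

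Two things follow. Part of the inequality can be taken out of the adjusted estimate, or added to it, depending on how smoking relates to the outcome. And if smoking or drinking shares unmeasured causes with weight or health, the adjusted coefficient is not a clean direct association either. With about 500 000 women sampling error is small, so the choice of covariates can matter more than chance for a small difference.

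**Working it through.** **The plan's own figures.** The protocol gives no figure on covariate roles. The nearest are its detectable differences at 0.015 SD:
- BMI: 0.015 × 4.8 = 0.072, stated as 0.07 kg/m2
- weight gain: 0.015 × 4 = 0.06 kg, as stated
- self-reported health: 0.015 × 0.3 = 0.0045, stated as 0.005 points

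The conversions are right. (The stated 95% power is conservative: 500 000 women with the 27% migrant share from the background section give 99.7%, two-sided. This does not bear on the point.)

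**Time order, exposure by exposure.**
- Country of birth: fixed before any smoking or drinking. Neither can be a cause of it.
- Education: generally completed or largely set before the smoking and drinking recorded around pregnancy. Both are plausibly downstream.
- Occupation: smoking or alcohol may come before unemployment, sick leave or disability pension, so they may be genuine confounders here. The order is unclear.

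**Do the t-tests supply the missing contrast?** They leave out smoking and alcohol, but also maternal age and every other true confounder, and they are planned for continuous outcomes only. The protocol names no model adjusted for true confounders alone.

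**Size of the shift.** In a linear model the unadjusted minus the adjusted contrast equals Δp × b. Here Δp is the difference in smoking prevalence between exposure groups and b is the difference in outcome between smokers and non-smokers. The protocol gives neither, so both are assumed:
- low: 0.05 × 0.5 = 0.025 kg or kg/m2
- high: 0.15 × 1.0 = 0.15 kg or kg/m2
- wider range for weight gain: 0.02 × 0.2 = 0.004 kg up to 0.15 kg

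In the protocol's SD units the high value is 0.15 / 4 = 0.0375 SD of weight gain and 0.15 / 4.8 = 0.031 SD of BMI. The low value is 0.025 / 4 = 0.006 SD and 0.025 / 4.8 = 0.005 SD. No figure is offered for alcohol.

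**Direction.** The sign is that of Δp × b. If the less educated group smokes more and has the higher BMI while smokers weigh less, adjustment widens the BMI gap. If that group reports worse health and smokers do too, adjustment narrows the health gap. If a migrant group smokes less, the signs reverse.

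**Shared unmeasured causes.** An illustrative simulation, with every parameter assumed, used 4 000 000 women, 27% of them exposed. The log-odds of smoking were −2.5 + 0.8 × exposure + 0.5 × U. The outcome was 0.3 × exposure + 0.5 × smoking + 1.0 × U + noise (SD 3.8), with U an unmeasured standard normal cause.
- Smoking prevalence differed by 0.082, so the total is about 0.30 + 0.5 × 0.082 = 0.341.
- Estimated without smoking: 0.339.
- Estimated with smoking: 0.258.

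The adjusted value misses both the total and the direct effect of 0.30. The simulation standard error is about √(3.8² + 1²) / √(4 000 000 × 0.27 × 0.73) = 3.93 / 888 = 0.004, so this is not simulation noise. It shows that the distortion can occur, not how large it is in this registry.

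**The case against.** **The list is not a model.** It also holds visit dates, estimated dates of birth and the exposures education and occupation, which cannot all enter one model. Every listed variable is given a descriptive role too, and covariate sets by model are commonly left to a statistical analysis plan. This stands in part: a reader might infer that every final model adjusts for smoking and alcohol, and the text does not establish that. But the protocol does assign the role of confounder, and analysis of covariance and logistic regression are where confounders are used. The fault is a role stated wrongly, not a detail left for later.

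**Unadjusted comparisons are planned.** True for continuous outcomes. They are not the demographically adjusted contrast, and they do not cover weight status categories or weight gain classed against the recommendations.

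**The aims ask for associations, not total causal effects.** A smoking-adjusted association is an association. But the significance section asks whether inequalities exist between groups as they are, and an inequality among women of equal smoking and drinking is a narrower quantity.

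**Occupation.** A reader might extend the point to all exposures. The protocol's own categories argue against that, since smoking or alcohol can precede sick leave or unemployment. Dropping them there could add confounding. This objection stands in full.

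**Benchmark.** Because 0.15 is 2.5 times 0.06 kg and about 2.1 times 0.072 kg/m2, a reader might infer that the shift can exceed twice what the study counts as a difference. The protocol does not support this. Those figures illustrate power for migrant versus non-migrant women and are not relevance thresholds. The assumed smoking gap was chosen for low versus high education, and the low end, 0.025, is below both figures.

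**Other entries look worse placed.** Type of delivery, birth weight and stillbirth come after early-pregnancy BMI. That widens the problem with the list and does not remove this one.

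**Conclusion.** The point holds for country of birth, with the migrant groupings built on it, and for educational attainment. For these the protocol gives smoking and alcohol a role that the likely time order does not support. Models built on that role would not estimate the inequality named in the aims and the significance section. It does not hold as a claim about occupation, nor as a claim that all adjusted results will be affected.

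The direction and size cannot be derived from the protocol. On the assumed 5-15 points and 0.5-1.0 kg or kg/m2 the shift is 0.025-0.15, at most about 0.04 SD. That is small in absolute terms, but it is of the order of the differences the study says it can detect. The conclusion rests on smoking and drinking coming after birth country and, in general, after schooling. The size rests wholly on assumption. The matter affects how adjusted results are read and should be settled before analysis. It does not invalidate the study.

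**What to change.** - **Country of birth and education:** remove smoking and alcohol consumption from the confounder set of the main models and keep them as descriptive variables. Report a second, labelled model that includes them, read as the difference not accounted for by smoking and alcohol. Do not read it as a clean direct effect.
- **Occupation:** report both models and state that the time order is unclear. Do not present the model without smoking and alcohol as the correct estimate.

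**Cost:** a change of protocol wording and one extra model column. No new data are needed and nothing is lost. The downside is that readers used to smoking-adjusted estimates must look at the second model.

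### Birth weight, type of delivery and stillbirth are given the role of confounder for outcomes that precede them; if they enter the models, the adjusted contrasts can be biased

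*Protocol*

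**What the plan says.** The protocol section on covariates and descriptive variables opens: "Following variables will be considered as confounders in the analysis and will also be utilized as descriptive data". A single list follows. It includes "length of pregnancy, county council, maternity care unit, smoking, alcohol consumption" and then "type of delivery, infant sex, birth weight and date, stillbirth, dates for visits in maternity care and revisits after birth". No item is marked as descriptive only, and no item is tied to a particular outcome.

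The section on main outcomes includes BMI in early and late pregnancy, "Weight status categories in early pregnancy", GWG from the first maternity visit to a weighing after week 35 (in kg, against the IOM recommendations, and as z-scores), and "Self-reported health before, during and after pregnancy". The section on data analysis and power names t-tests, ANCOVA and logistic regression.

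The Background places some of the listed variables downstream of these outcomes. It links high BMI and excessive GWG to "increased risks for adverse pregnancy health outcomes such as gestational diabetes, preeclampsia, cesarean delivery and infant death", and says that "underweight and inadequate gestational weight gain have been associated with higher risks of low birth weight infants and preterm birth".

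**The concern.** A confounder of a migrant or socioeconomic contrast cannot be something that arises only after the outcome has been determined. Birth weight, type of delivery and stillbirth do not exist when early BMI or pre-pregnancy health is recorded, and they are recorded after the GWG interval has ended. For cesarean delivery and low birth weight, the Background itself treats BMI and GWG as the risk factors and the birth event as the result. The covariate section gives them the opposite role.

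Conditioning on a consequence of the outcome can distort the exposure contrast. If the groups differ in birth weight for reasons unrelated to GWG, adjusting for birth weight creates a GWG difference that is not there, or shifts one that is. A larger sample does not remove this bias. With about 500 000 women, even a small artefact can look precise, and the Significance section expects the results to inform clinical care and public health policy.

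**Working it through.** **Step 1. Order in time, outcome by outcome.**

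- *Early-pregnancy BMI and weight status; health before pregnancy:* birth weight, type of delivery, stillbirth and length of pregnancy all come later. None can confound.
- *Health during pregnancy:* birth weight, type of delivery and stillbirth come later.
- *GWG:* the last weighing precedes the birth. The Background presents low birth weight and cesarean delivery as outcomes for which GWG is a risk factor. It names infant death, not stillbirth, so the case for stillbirth rests on timing. Length of pregnancy is different: the time available to gain weight varies between women, so a duration term is defensible for GWG in kg.
- *Health after pregnancy:* birth weight, type of delivery and stillbirth come before the outcome. They are possible mediators, and adjusting for them removes part of the total contrast.

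**Step 2. The plan's own yardstick.** The protocol states a detectable difference of 0.015 SD and a GWG SD of 4 kg: 0.015 x 4 = 0.06 kg, as stated. With 500 000 women, 27 % migrants (Background) and two-sided alpha 0.05, the difference detectable with 95 % power is (1.960 + 1.645) x sqrt(1/135 000 + 1/365 000) = 0.0115 SD, or about 0.046 kg. The stated 0.06 kg is therefore on the cautious side. The point does not depend on it.

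**Step 3. Size of the bias for one case: GWG adjusted for birth weight.** Inputs from the protocol: GWG SD 4 kg, N = 500 000, 27 % migrants. Inputs assumed here and absent from the documents: birth-weight SD 0.5 kg; correlation r between GWG and birth weight of 0.15 to 0.30; a group difference c in birth weight, not due to GWG, of -50 to -150 g.

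Let d be the true group difference in GWG. In a linear model,

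adjusted contrast = d x (1 - r²) - r x (SD of GWG / SD of birth weight) x c.

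The SD ratio is 4 / 0.5 = 8. With d = 0:

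| r | c (kg) | Spurious GWG difference |
|---|---|---|
| 0.15 | -0.05 | 0.15 x 8 x 0.05 = 0.06 kg |
| 0.20 | -0.10 | 0.20 x 8 x 0.10 = 0.16 kg |
| 0.30 | -0.15 | 0.30 x 8 x 0.15 = 0.36 kg |

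For the middle row, the standard error is about 4 x sqrt(1 - 0.04) / sqrt(500 000 x 0.27 x 0.73) = 0.0125 kg, so z = 0.16 / 0.0125 = 12.8. With the same r and c and a true difference of -0.5 kg, the adjusted value is -0.5 x 0.96 + 0.16 = -0.32 kg. A least-squares simulation with N = 500 000 and 27 % migrants gave 0.05 to 0.35 kg under the null, in line with the formula.

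**Step 4. Sensitivity to the assumptions.** In SD units, with r of 0.1 to 0.3 and c of -0.1 to -0.3 SD, the spurious difference is r x |c| = 0.01 to 0.09 SD, that is 0.04 to 0.36 kg. The low end lies below the plan's 0.06 kg. If c = 0, there is no bias under the null. A true difference then only shrinks, by a factor of 1 - r²; for a true 0.2 SD, the loss is 0.2 x 0.01 = 0.002 to 0.2 x 0.09 = 0.018 SD.

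**The case against.** The strongest reply is that the section does not fix an adjustment set. The wording may name candidates only. The list also holds items that are not natural model terms, such as visit dates and two estimates of the due date, and it repeats education and occupation, which are main exposures elsewhere. It could be a registry-extraction list, with the model for each outcome left to a statistical analysis plan that is not shown. The protocol also plans unadjusted t-tests, states its aims as associations and names no primary model.

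This stands as a limit on the claim: the bias arises only if the variables enter the models. It does not remove the point. The text assigns every item the confounder role, and for these three variables that role is wrong even as a candidate. A data-driven selection would tend to keep a strong correlate such as birth weight.

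A reader might infer more than the documents support:

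- *That infant sex is also a consequence of BMI or GWG.* Nothing in the Background says so, and it is fixed at conception.
- *That length of pregnancy is wrong everywhere.* It is defensible as a duration term for GWG in kg.
- *That the delivery variables are consequences of health after pregnancy.* They precede it.
- *That the Background proves causation.* It speaks of associations and risk factors.

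**Conclusion.** The point holds for birth weight, type of delivery and stillbirth as confounders of early BMI and weight status, health before and during pregnancy, and GWG. It also holds for length of pregnancy with early BMI and pre-pregnancy health. For health after pregnancy the issue is adjustment for possible mediators.

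The structural error follows from the protocol's text. The size does not: 0.06 to 0.36 kg rests on three assumed inputs and covers only birth weight on GWG. No size is offered for the other outcomes or for type of delivery and stillbirth. The yardstick of 0.06 kg is a detection limit, not a difference of clinical importance. It would go too far to say that the adjusted results will be wrong, or that an artefact is certain to be statistically significant. Both depend on what enters the models and on group differences that the documents do not give.

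**What to change.** In the covariate section, replace the single list with an adjustment set for each outcome, limited to variables that precede it, for example maternal age, parity, single or multiple pregnancy, calendar year and county. Then:

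- Make birth weight, type of delivery, stillbirth and post-birth revisit dates descriptive only, or use them only in labelled mediation or sensitivity analyses, for example for health after pregnancy.
- Drop length of pregnancy from the models for early BMI and pre-pregnancy health. For GWG in kg, use gestational age at each weighing, which can be derived from the visit dates and due-date estimates already listed.
- Infant sex need not be excluded.

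The cost is a wording change and slightly more model specification. No new data are needed.
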